# Dovramilast for Erythema Nodosum Leprosum in Patients With Leprosy in Nepal: Protocol for a Phase 2 Open-Label Pilot Study

**DOI:** 10.2196/88069

**Published:** 2026-06-17

**Keywords:** CC-11050, clinical trial, dovramilast, erythema nodosum leprosum, ENL severity scale, leprosy, Nepal

## Abstract

**Background:**

Erythema nodosum leprosum (ENL) is an immunological complication affecting up to 10% of borderline lepromatous and 50% of lepromatous leprosy cases with a high bacterial index (3‐6+). Current treatments often require prolonged therapy over years and cause significant long-term side effects, highlighting the need for new therapies. Therefore, it is imperative to identify new therapies for ENL. Phosphodiesterase 4 inhibitors are a class of compounds that mediate immune homeostasis and have the potential to treat ENL with fewer side effects. Dovramilast (formerly CC-11050) is an anti-inflammatory phosphodiesterase 4 inhibitor; to date, it has been shown to be well tolerated in phase 1 human studies. This is the first phase 2 study of dovramilast in ENL.

**Objective:**

This phase 2 pilot study aims to assess the safety and tolerability of dovramilast and to explore preliminary clinical responses in patients with new or recurrent ENL.

**Methods:**

This study was designed in two steps: (1) 28 days of treatment for 10 males to ensure safety and (2) an initial 12-week treatment course, with the option to retreat if further ENL episodes occur (up to 48 wk of treatment), for up to 40 males or females, as required on a case-by-case basis. Demographic, clinical, and laboratory data will be collected longitudinally, along with the ENL International Study Group ENL Severity Scale, Brief Pain Inventory, and Douleur Neuropathique 4 questionnaire for the identification of neuropathic pain. Patients will be followed for 12 months for ENL recurrence after cessation of the study drug. Safety will be evaluated through adverse event reporting and laboratory monitoring, while efficacy will be assessed using descriptive and trend-based analyses of changes in ENL severity, pain, and clinical outcomes over time.

**Results:**

The initial safety evaluation (step 1) of this phase 2 pilot study was completed and reviewed by an independent Data Safety Monitoring Board, which did not identify safety concerns that would preclude continuation of the study. Based on the step 1 results, the study proceeded to step 2, which evaluates longer-term administration of dovramilast in male and female participants. As of April 2026, a total of 15 participants have been recruited. All study data are anticipated to be collected by September 2027, with publication of the main trial results expected by December 2027.

**Conclusions:**

This phase 2 pilot study is designed to generate preliminary data on the safety, tolerability, and potential clinical signals of dovramilast in patients with new or recurrent ENL. Findings from this exploratory trial will inform the feasibility, outcome measures, and design of future adequately powered randomized controlled studies and do not directly support changes to current clinical practice at this stage.

## Introduction

### Leprosy and Leprosy Reactions

Leprosy is an important but neglected global disease. Effective multidrug therapy (MDT) has resulted in a reduced prevalence of the disease, and leprosy case detection rates have stagnated over recent decades, as reported by the World Health Organization (WHO) [1,2]. Leprosy is caused by the acid-fast bacteria *Mycobacterium leprae* or *M. lepromatosis* and primarily affects the skin and peripheral nerves [3,4].

In 2023, 72.9% of new leprosy cases detected were multibacillary [1] presenting with one or more cardinal signs, including greater than 5 lesions, detectable *M. leprae* bacilli, or peripheral nerve involvement, compared to paucibacillary presenting with less than 5 lesions and no detectable bacilli [5]. Delayed diagnosis or treatment of leprosy can lead to permanent nerve damage and disabling deformities. Neuropathy may develop before, during, or long after treatment due to persistent mycobacterial antigens that drive immunological reactions and accelerate nerve injury. Consequently, leprosy reactions are a major contributor to long-term disability in affected individuals [6-12].

Two major types of leprosy reactions occur, affecting up to 30% to 50% of all leprosy cases at some point: type 1 reaction (T1R, reversal reaction) and erythema nodosum leprosum (ENL, also called type 2 reaction) [7,13-15]. T1R typically involves increased cell-mediated immunity toward leprosy antigens and most often develops in borderline tuberculoid, borderline borderline, and borderline lepromatous (BL) cases. However, ENL develops only in BL and lepromatous leprosy (LL) cases, with high bacterial loads associated with reduced T cells and increased antibody responses to leprosy antigens. ENL may occur before the start of leprosy treatment but can also develop during or years after MDT [6,7]. After treatment for leprosy, people may experience episodes of ENL for years because mycobacterial antigens persist despite bactericidal MDT [6-8,16]. Neuritis can occur either alone or in combination with T1R or ENL. Some patients experience reaction cases typical of T1R and ENL in succession or in combination [17,18].

### Characteristics of ENL

ENL presents as new, red, painful nodules, usually on the legs, arms, face, and sometimes on the trunk, and it varies in severity [8,19-22]. It is characterized by the rapid appearance of successive crops of painful and erythematous subcutaneous nodules that may ulcerate [19]. ENL may be present at the time of leprosy diagnosis or develop within the first few years after starting MDT [6-8].

Individual ENL episodes can last months or years, with a significant proportion of patients experiencing recurrent episodes [6,8]. Recurrent ENL reactions are defined as more than 1 ENL episode with the same characteristics as acute ENL. Chronic ENL is defined as an episode lasting for more than 6 months of treatment. The main risk factors for ENL are LL or BL leprosy with high bacterial load and a bacterial index greater than or equal to 3+ [11,19,23]. Of these, 10% of patients with BL and 50% of patients with LL develop the first ENL episode coincident with leprosy diagnosis, during MDT, or in the years after MDT completion. Other less well-defined factors that increase risk include pregnancy, lactation, puberty, intercurrent infection, vaccination, and stress [16].

Systemic signs and symptoms, such as fever, anorexia, and malaise, signal its occurrence; however, these symptoms are not always recognized in association with leprosy and can be initially misdiagnosed [19]. See Figure 1 for symptoms and organ systems that are variably associated with ENL. The ENL International Study Group ENL Severity Scale (EESS) focuses on a subset of 10 major symptoms as severity indicators common to both males and females: pain, fever, number of ENL lesions, inflammation of ENL lesions, extent of ENL lesions, peripheral edema, bone pain, inflammation of joints and/or digits, lymphadenopathy, and nerve tenderness [19,24].

**Figure 1. F1:**
[figure not shown]
Symptoms and organ involvement associated with erythema nodosum leprosum (ENL). The peripheral nervous system is shown on the left and the lymphatic system on the right. Symptoms and incidence are consolidated from reviews and ENL cohort reports [19,25]. Created in BioRender by author [name] [26].

When the reaction is mild, only the skin is affected, often in combination with a low-grade fever. When the reaction is severe, the nodules are multiple and may ulcerate, there may be a high fever, and other organs such as the nerves, eyes, joints, testes, and lymph nodes may be inflamed. Typically, recurrence in these patients presents with the emergence of red subcutaneous swelling, often associated with fever and pain.

Apart from disability and stigma, ENL can cause devastating psychosocial, physical, and economic hardship [9,27,28] and multiple hospitalizations in affected patients. Moreover, the side effects of treatments create vulnerabilities to other diseases, prevent patients from leading normal social or emotional lives or engaging with others, cause loss of employment or cessation of schooling, or degrade their enthusiasm to struggle against these obstacles.

### Potential Causes of ENL

The pathogenesis of ENL is poorly understood [14,29,30]. ENL was previously considered to be an immune complex–mediated phenomenon; however, very limited and sometimes contradictory evidence is available to support this [31].

As is common in BL or LL cases, studies have indicated that ENL patients have high levels of anti*–M. leprae* antibodies, as well as persistent levels of *M. leprae* antigens. The most characteristic feature of the lesions is the presence of a neutrophilic infiltrate. Immunoglobulin and complement deposition are present in the skin lesions. Serum complement levels are decreased, and the expression of interleukin (IL)-6, IL-8, IL-10, IL-4, and IL-5 is increased. Activation of both toll-like receptor 2 and fragment crystallizable receptors has been shown to induce IL-1β, which upregulates the expression of E-selectin and neutrophil binding in endothelial cells. Additionally, neutrophils can be stimulated by *M. leprae* to secrete tumor necrosis factor (TNF)-α and IL-8, thereby increasing inflammation [14,29,30].

Cell-mediated immune responses also contribute to the pathogenesis of ENL. Several studies have supported the association of a T-helper 1-type response with high levels of interferon-gamma and IL-12 [30]. CD4^+^ T cells have been shown to outnumber CD8^+^ T cells by 2 to 1. On the other hand, other studies have suggested that a T-helper 2-type response dominates, with high levels of TNF-α and IL-6 detected in the serum and skin lesions [10,32]. More recently, single nucleotide polymorphisms in the IL-6 gene were found to be associated with ENL [33]. Soil-transmitted helminth–induced immunomodulation across many shared cellular and cytokine pathologies may also be relevant to the development of neuritis, T1R, and ENL reaction episodes in coendemic populations [34].

### Treatment for ENL

Prednisolone, thalidomide, and clofazimine are currently recommended by the WHO as treatment for ENL; however, ENL treatment has been controversial for decades [20,21,28,35,36]. Prednisolone is the most common first-line treatment in most low- or middle-income countries and leprosy-endemic countries (except Brazil, which uses thalidomide). Prednisolone is generally available and affordable, but, as ENL may require years of treatment, patients can develop severe consequences such as diabetes, cardiovascular problems, blindness, and osteoporosis leading to bone fractures [37-39].

Thalidomide, the most recently recommended therapeutic agent for the treatment of ENL, was developed more than 50 years ago and has both immunoregulatory and sedative activity [40]. However, owing to the teratogenicity and related consequences in the 1960s, thalidomide is often restricted or unaffordable for most ENL cases in endemic countries. High-dose clofazimine has anti-inflammatory properties and can be given in combination with prednisolone. Studies, however, have not indicated a significant impact, and patients rarely tolerate clofazimine due to skin pigmentation [41].

Both high-dose prednisolone and thalidomide are sometimes insufficient to control severe refractory ENL [42-44]. Many cases are chronic and experience ENL symptom relapse soon after the decrease in dosage or cessation of drugs [35]. Thus, a safe and effective drug that can be used for a shorter duration and imparts long-term remission has always been envisioned [28]. These problems are compounded by the lack of alternative treatments with established efficacy for ENL. Various efforts have been made to develop alternative ENL treatments, most notably pentoxifylline, azathioprine, cyclosporine, methotrexate, and anti-TNF biologics such as etanercept and infliximab [45-59].

### Dovramilast in Relevance to ENL

Dovramilast has been evaluated as an adjunct host-directed therapy in HIV, tuberculosis, and SARS-CoV-2 infection models and clinical studies, demonstrating immunomodulatory effects and a favorable safety profile [60-67]. Preclinical studies in rabbit and mouse models of tuberculosis showed improved bacterial clearance and reduced lung inflammation and fibrosis. Phase 1 and phase 2 clinical trials in HIV and tuberculosis patients confirmed good tolerability with no serious adverse events (AEs) and evidence of improved clinical outcomes [60,64,67]. Although previously studied as an adjunct host-directed therapy in infectious diseases, ENL represents a distinct immunological complication, supporting the rationale for evaluating dovramilast as a novel therapeutic option distinct from thalidomide [36,68,69]. The structural difference between dovramilast and thalidomide is presented in Figure 2.

**Figure 2. F2:**
[figure not shown]
Chemical structures of dovramilast and thalidomide. Figures were drawn using the RCSB PDB Chemical Sketch Tool with chemical Simplified Molecular-Input Line-Entry System (SMILES) from PubChem.

Therefore, the primary objective of this phase 2, open-label clinical trial is to evaluate the safety and preliminary efficacy of dovramilast in adults with new or recurrent ENL. The primary research question is whether dovramilast is safe and well tolerated when administered for short- and longer-term treatment cycles in patients with ENL. Secondary research questions address whether dovramilast treatment is associated with improvements in ENL severity, pain, and clinical manifestations over time, and whether repeated treatment cycles can reduce recurrence without the need for prolonged corticosteroid or thalidomide use. We hypothesize that dovramilast will demonstrate a favorable safety profile and lead to clinically meaningful reductions in ENL severity and symptom burden, supporting its further evaluation as an alternative therapeutic option for ENL.

This protocol is written based on SPIRIT (Standard Protocol Items: Recommendations for Interventional Trials) guidelines (Checklist 1) [70].

## Methods

### Research Question and Hypothesis

The primary research question of this phase 2 pilot study is whether dovramilast is safe and well tolerated in patients with new or recurrent ENL. Secondary research questions explore whether dovramilast treatment is associated with improvements in ENL severity, pain, and clinical manifestations over time and whether repeated treatment cycles may reduce recurrence. Given the exploratory nature of this pilot study, formal hypothesis testing is not planned; instead, the study is designed to generate preliminary safety, feasibility, and clinical trend data to inform future randomized controlled trials.

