**Figure 4. F4:**
[figure not shown]
List of laboratory tests to be performed during the trial. The asterisk (*) indicates the subset of tests performed in step 1. All tests will be performed in step 2. Created in BioRender [26].

Study participants will be eligible for any concomitant treatment, including, but not limited to, WHO-recommended MDT, antipyretics, and analgesics. No standard ENL treatment regimens of prednisolone or thalidomide, or both, will be provided during the study drug treatment. In step 1, any new ENL episodes after the cessation of the study drug will be managed with standard ENL care. In step 2, any new ENL episodes will be managed with a repeat 12-week treatment cycle with dovramilast.

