#### Step 2: Evaluation of the Long-Term Effects

Participants will be either male or female, aged 18 to 65 years, with a new or newly recurrent ENL episode and will receive 200 mg of dovramilast twice daily. Male weights will be aligned with step 1 requirements (≥40 kg), whereas females should weigh at least 35 kg.

In a subset of participants during step 2, pharmacokinetic assessments of drug levels in the blood will be performed using plasma collected at appropriate times on day 1 and day 10 (predose and 3 hours postdose) after dovramilast treatment.

As in step 1, participants will be enrolled for an initial 7 to 10 days of treatment. If patients tolerate the drug well and respond, they will continue to receive dovramilast for 12 weeks.

Every 12 weeks of treatment, dovramilast will be discontinued to determine if ENL symptoms recur or if the ENL episode has fully recovered. If symptoms recur after 28 days within the 1-year follow-up period, dovramilast will be administered again for another 12 weeks, as indicated by individual patient needs, for up to 1 year of total dovramilast treatment duration (12 wk × 4=48 wk total). Based on individual patient clinical needs, this discontinuation test will be repeated at 6 and 9 months for a total treatment period of up to 52 weeks. While clinical care may occur more frequently as indicated by individual ENL symptoms, participants will be evaluated on days 10 and 28 and monthly during treatment, and monthly for 1 year after discontinuation of the drug (final visit).

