### Primary and Secondary Outcomes

The primary outcome is the proportion of participants achieving a complete clinical response by day 10 of dovramilast treatment. Complete clinical response is defined as a clinically meaningful improvement or resolution of ENL manifestations based on standardized clinical criteria rather than a binary presence or absence. This includes a reduction in the number, tenderness, and inflammation of ENL skin nodules, assessed clinically and supported by changes in the EESS score; resolution of ENL-associated fever based on clinical assessment and temperature recordings; and improvement or resolution of nerve pain and tenderness evaluated through neurological examination and validated pain assessment tools. Safety outcomes include the frequency and severity of AEs, graded according to the National Cancer Institute Common Terminology Criteria for Adverse Events (NCI CTCAE) version 5.0 [71], as well as laboratory abnormalities and neurological assessments. In addition, plasma and skin biopsy samples will be collected at predefined time points for exploratory evaluation of biological responses to dovramilast, including inflammatory and immunological markers relevant to ENL pathogenesis (such as circulating cytokines, acute-phase reactants, and immune cell–associated markers), and histopathological features of ENL lesions. These exploratory analyses will be descriptive and are intended to provide mechanistic insights into treatment response.

Secondary outcomes include the proportion of participants who achieve and maintain remission of ENL symptoms during treatment and for up to 12 months following cessation of the study drug. Longitudinal changes in disease severity, pain, and neurological symptoms will be assessed over time using validated instruments, including the EESS, Brief Pain Inventory, and Douleur Neuropathique 4 questionnaire. In addition, the frequency of ENL recurrence and the need for repeat dovramilast treatment cycles during the follow-up period will be documented.

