### Interventional Methods

Step 1: twice-daily administration of 200 mg of dovramilast to be taken with fatty food. The treatment will be for 10 days, with a rollover for a total of 28 days if safety and efficacy demonstrate benefit by day 10 for the patient. Step 2: twice-daily administration of 200 mg of dovramilast in patients to be taken with fatty food for 12 weeks, with additional 12-week treatment cycles (week 48) depending on individual clinical needs.

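### The design cannot identify whether repeated cycles reduce recurrence, because in step 2 a repeat cycle is given in response to a recurrence

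*Protocol article*

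**What the plan says.** The question appears twice. Methods, Research Question and Hypothesis, sets out to explore "whether repeated treatment cycles may reduce recurrence". The last part of the Introduction (Dovramilast in Relevance to ENL, after Figure 2) words it more strongly: "whether repeated treatment cycles can reduce recurrence without the need for prolonged corticosteroid or thalidomide use".

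The rule for giving a repeat cycle appears in several places:
- Study Design, Overview: "In step 2, any new ENL episodes will be managed with a repeat 12-week treatment cycle with dovramilast".
- Step 2: Evaluation of the Long-Term Effects: "If symptoms recur after 28 days within the 1-year follow-up period, dovramilast will be administered again for another 12 weeks", up to four cycles ("12 wk × 4=48 wk total").
- The Abstract also ties retreatment to further episodes.
- Interventional Methods is looser: "with additional 12-week treatment cycles (week 48) depending on individual clinical needs".

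The Overview describes a single-arm, open-label trial. Recurrences in step 1 (10 men, 28 days of drug) go to standard care.

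What is to be measured and analysed is more modest than the question. Under Primary and Secondary Outcomes, "the frequency of ENL recurrence and the need for repeat dovramilast treatment cycles during the follow-up period will be documented". Data Analysis plans the frequency and timing of recurrences as a description of durability. Strengths and Limitations concedes that the single-arm design and the sample size rule out formal efficacy comparisons, but does not mention that retreatment is triggered by recurrence.

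**The concern.** Asking whether repeated cycles reduce recurrence is asking what retreatment does compared with not retreating. Here the exposure (another cycle) is brought about by the outcome it is supposed to reduce (a recurrence), and the trial has no participants who recur in step 2 and are assigned to no repeat cycle. The difficulty is one of identification, so neither a larger sample nor a formal test would remove it.

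At stake is what the trial may conclude under this question. A falling recurrence rate over successive cycles could be reported as benefit from repeating treatment, and a rising one as loss of effect. Neither reading would be sound. Future Directions says the findings will inform, among other things, treatment duration in later randomized trials, so a misread trend could carry forward.

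**Working it through.** The plan gives no figure for this question, so there is none to reproduce. The check has a structural part, which needs no assumed numbers, and an illustration, which does.

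**Structure.** Taking the step 2 rule at face value (retreat when there is a recurrence, at most four cycles):

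number of cycles = 1 + number of recurrences, until the cap of 4.

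Participants with 1, 2 or 3 cycles then have 0, 1 or 2 recurrences, and those with 4 cycles have 3 or 4. A simulation of this rule with no effect of repeat cycles (400,000 participants per scenario; mean recurrence risk 0.3, 0.5 or 0.7; varying heterogeneity and natural decline) gives a correlation between cycles and recurrences of 0.985 to 0.998. That association comes from the rule alone. In practice the mapping is looser, as set out under the objection.

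**Comparing successive cycles.** Assume that repeat cycles have no effect, that each participant has a personal recurrence risk p drawn from Beta(a, b), and that risk changes naturally by a factor d per cycle. Only those who recur go on. Among those who receive cycle c,

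recurrence after cycle c = d^(c−1) × (a + c − 1)/(a + b + c − 1).

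For Beta(2,2):
- d = 1: 2/4, 3/5, 4/6, 5/7 = 0.500, 0.600, 0.667, 0.714. Entering cycle 4: 40 × 0.500 × 0.600 × 0.667 = 8.0.
- d = 0.7: multiply the same fractions by 1, 0.7, 0.49, 0.343 = 0.500, 0.420, 0.327, 0.245. Entering cycle 4: 40 × 0.500 × 0.420 × 0.327 = 2.7.

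The same formula over a wider range:

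| Assumed risk | d | Recurrence after cycles 1, 2, 3, 4 | Of 40, entering cycles 2, 3, 4 |
|---|---|---|---|
| Beta(2,2), mean 0.5 | 1 | 0.500, 0.600, 0.667, 0.714 | 20.0, 12.0, 8.0 |
| Beta(2,2), mean 0.5 | 0.7 | 0.500, 0.420, 0.327, 0.245 | 20.0, 8.4, 2.7 |
| Beta(1,1), mean 0.5, wide spread | 1 | 0.500, 0.667, 0.750, 0.800 | 20.0, 13.3, 10.0 |
| Beta(50,50), mean 0.5, almost no spread | 0.6 | 0.500, 0.303, 0.184, 0.111 | 20.0, 6.1, 1.1 |
| Beta(0.6,1.4), mean 0.3 | 1 | 0.300, 0.533, 0.650, 0.720 | 12.0, 6.4, 4.2 |
| Beta(1.4,0.6), mean 0.7 | 0.6 | 0.700, 0.480, 0.306, 0.190 | 28.0, 13.4, 4.1 |

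With no effect of repeat cycles in any row, the rate rises where selection dominates and falls where natural decline dominates. The direction of an observed trend therefore says nothing certain about retreatment.

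**Step 1 as a comparator.** It does not fill the gap. It had 10 men on a 28-day course, was completed in 2020, and was neither concurrent nor randomized against step 2.

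**The case against.** The best defence is that the operative sections already stay within what the design can deliver. Aims and Objectives speaks of documenting remission and recurrence, the outcomes and Data Analysis do likewise, no hypothesis test is planned, the Methods wording is hedged, and the Conclusions disclaim definitive efficacy. This stands, and it confines the error to the stated question and to conclusions drawn under it. It does not make the question answerable: a descriptive rate carries the same bias as a tested one, and the limitation that is conceded does not name the recurrence trigger.

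A reader might infer more than the documents support in four ways:
- *That the plan itself compares later cycles with cycle 1.* It does not. Data Analysis lists frequency and timing only, so the misleading comparison is a risk in reporting and not a planned analysis.
- *That one cycle always means no recurrence.* That is not exact. A one-cycle participant may recur before 28 days, stop because of an adverse event, or miss visits, and the wording on individual clinical needs leaves room for judgement. These routes loosen the mapping and add selection; they do not restore a comparison.
- *That the future trial's treatment duration will be chosen from these rates.* Future Directions says only that findings will inform the design, duration included.
- *That the whole Introduction question fails.* The part on avoiding prolonged corticosteroid or thalidomide use can be described in one arm.

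The method for summarising recurrence times is commonly left to an analysis plan, so its absence from the article is not a fault. The durability summary suggested below is a recommendation.

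**Conclusion.** The concern holds in this form: the effect of repeated cycles on recurrence, asked about in the Introduction and the Methods, cannot be identified from a single arm in which recurrence triggers the repeat cycle. No analysis plan can supply the missing contrast. That conclusion follows from the protocol's own rule and needs no assumed figures.

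The size of any misleading trend is not known. The recurrence risks, their spread and the natural decline are all assumptions, as is full enrolment of 40 in step 2, where the plan says up to 40 and reports 15 participants recruited by April 2026. The figures show that a rise or a fall is possible with no effect and that few participants would inform the later cycles (about 1 to 10 of 40 entering cycle 4 across the rows shown). They do not predict what this trial will see.

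Because the question is secondary and the analysis already descriptive, this should be corrected but does not threaten the trial's primary purpose.

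**What to change.** 1. In the Introduction and in Research Question and Hypothesis, reword the recurrence part of the question to: *describe the frequency and timing of recurrence after each treatment cycle*. Keep the descriptive part on corticosteroid or thalidomide use.
2. In Data Analysis, make the durability summary the time from stopping cycle 1 to first recurrence, in everyone who stopped cycle 1, with censoring for incomplete follow-up. This group is not selected on having recurred in the study.
3. Present later cycles by cycle number, with the denominator for each.
4. Add to Strengths and Limitations that, because retreatment is triggered by recurrence, these data do not show an effect of repeated cycles.

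The cost is wording plus one time-to-event summary, built from recurrence timing that the plan already documents. The retreatment rule, visits and data collection stay as they are. Data collection is expected to run to September 2027, so the change can still be made before the main analysis. The downside is a more modest secondary question.
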